#### Transmission of infectious diseases

Standard procedures to prevent infections, which can be transmitted by drugs derived from blood or plasma, include the selection of the donor, testing of the single donation and the plasma pool for specific infectious disease markers.

Nevertheless, when using drugs derived from human blood or plasma, infectious diseases transmitted by agents - even from unknown nature so far - cannot completely be ruled out. In case of an occurrence of an infectious disease this has to be treated according to the underlying diagnosis.

### **Follow up 1-2 weeks after CIK cell infusions**

Before, one hour, one and two weeks after CIK cell infusion the patients will be monitored for immune responses. Therefore 7.5 – 10 mL of EDTA blood will be taken at above mentioned time points for assessment of blood counts, numbers of CD3-, CD4-, CD8-, CD56-, CD14-positive cells, cytokine release and tumor escape mechanisms. Blood samples will be gathered by stem cell laboratory:

University Hospital Frankfurt, Goethe University  
Department for Children and Adolescents  
Division for Stem Cell Transplantation and Immunology  
Stem Cell Laboratory (House 32D)  
[name]  
[contact], [contact]

**Follow up 2-4 weeks after CIK cell infusions** (CIK cell infusions will be continued until patient reaches molecular remission, until a maximum of 8 infusions are reached, until the patient progresses or discontinuation criteria are met):

- History taking\*
- Physical examination\*
- Karnowsky/Lansky performance index\*
  
- Body weight\*
- Peripheral blood
  - Blood count\*
  - Bilirubin\*
  - Chimerism (monthly\*)
- Bone marrow (every 3 months\*)
  - Morphology or histology
  - Chimerism, including subpopulations if appropriate
  - MRD if appropriate
  - BCR-ABL/ABL ratio if appropriate

\* Obligatory

### **Eligibility requirements for next CIK cell infusion (4-6 weeks after previous CIK cell infusion):**

- No immunosuppression or steroids
- No chemo- or immune therapy, except patients with tyrosine-kinase inhibitors (TKI) for BCR-ABL positive leukemias.

### **Follow up after last CIK cell infusion:**

**Within one month and thereafter every three months:**

- History taking\*
- Physical examination\*
- Karnowsky/Lansky performance index\*
- Peripheral blood
  - Blood count\*
  - Bilirubin\*
  - Immune status (optional)
  - Chimerism\*
- Bone marrow (optional)
  - Morphology or histology

Chimerism, including subpopulations if appropriate  
MRD if appropriate  
BCR-ABL/ABL ratio if appropriate

#### **Once a year**

- Ophthalmologist control
- Pulmonary function testing
- \* Obligatory

Other laboratory investigations will be performed as per routine clinical care after allogeneic SCT according to institutional guidelines.

Acute and chronic GvHD will be graded according to the Glucksberg scale (see Appendix 1)

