| Physical examination                                                                      | x                            |  |  | x                          |   | x   |                                                                                                                                                                                                    |     |     |     |     | x                                                                                                      |
| GvHD acc. to Glucksberg
Seattle Criteria                                               | x                            |  |  |                            |   | x   |                                                                                                                                                                                                    |     |     |     |     |                                                                                                        |
| Lansky/Karnofsky index                                                                    | x                            |  |  |                            |   | x   |                                                                                                                                                                                                    |     |     |     |     | x                                                                                                      |
| Body weight                                                                               | x                            |  |  |                            |   | x   |                                                                                                                                                                                                    |     |     |     |     |                                                                                                        |
| Cell infusion                                                                             |                              |  |  | x              |   |     | x                                                                                                                                                                                      |     |     |     |     |                                                                                                        |

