### **2.3 Primary Endpoints**

- The dose-limiting toxicity based on grade III or IV acute GvHD
- Chronic extensive GvHD

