#### Glucksberg acute GvHD scores

##### Skin

- Stage 0: No rash
- Stage 1: Maculopapular rash <25% of body surface area
- Stage 2: Maculopapular rash on 25-50% of body surface area
- Stage 3: Generalized erythroderma
- Stage 4: Generalized erythroderma with bullous formation and desquamation

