##### GI

- Stage 0: No diarrhea, or diarrhea <500 mL/day
- Stage 1: Diarrhea 500-999 mL/day
- Stage 2: Diarrhea 1000-1499 mL/day
- Stage 3: Diarrhea >1500 mL/day
- Stage 4: Severe abdominal pain, with or without ileus

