#### **CLINICAL EXTENSIVE cGvHD**

1. Involvement of two or more organs with symptoms or signs of cGvHD, with biopsy documentation of cGvHD in any organ >15% base line body weight loss not due to other causes, with biopsy documentation of cGvHD in any organ
2. Skin involvement more extensive than defined for clinical limited cGvHD, confirmed by biopsy
3. Scleroderma or morphea
4. Onycholysis or onychodystrophy thought to represent cGvHD, with documentation of cGvHD in any organ
5. Decreased range of motion in wrist or ankle extension due to fasciitis caused by cGvHD
6. Contractures thought to represent cGvHD
7. Bronchiolitis obliterans not due to other causes
8. Positive liver biopsy; abnormal liver function tests not due to other causes with alkaline phosphatase >2 x upper limit of normal, AST or ALT >3 x upper limit of normal, or total bilirubin >1.6, and documentation of cGvHD in any organ
9. Positive upper or lower GI biopsy

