| Eyes         | Dryness, burning, blurring, gritty eyes, photophobia, pain                                                                                                                                                                                                                                       |
| Vagina/vulva | Dryness, dyspareunia, stricture or stenosis, erythema, atrophy or lichenoid changes not induced by ovarian failure                                                                                                                                                                               |
| Liver        | Elevated liver function tests not due to other causes (alkaline phosphatase $\geq 3$ x upper limit, of normal, AST or ALT $>4$ x upper limit of normal or total serum bilirubin $\geq 2.5$ ; in the absence of cGvHD involving other organs, liver biopsy is required to confirm the diagnosis)  |
| Lung         | Bronchiolitis obliterans (see diagnostic indicators), cough, wheezing, dyspnea on exertion, history of recurrent bronchitis or sinusitis                                                                                                                                                         |
| GI           | Anorexia, nausea, vomiting, weight loss, diarrhea, dysphagia, odynophagia, malabsorption                                                                                                                                                                                                         |
| Fasciitis    | Stiffness and tightness with restriction of movement, occasionally with swelling, pain, cramping, erythema and induration, most commonly affecting the forearms, wrists and hands, ankles, legs and feet, inability to extend the wrists without flexing the fingers or the elbows, contractures |
| Muscle       | Proximal muscle weakness, cramping                                                                                                                                                                                                                                                               |
| Skeletal     | Arthralgia of large proximal girdle joints and sometimes smaller joints                                                                                                                                                                                                                          |

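### Extensive chronic GvHD is a primary endpoint, but the text sends it to an acute-only scale and lists no GvHD grading at the quarterly visits after the last infusion

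*Protocol*

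**What the plan says.** Protocol section 2.3 lists two primary endpoints: "The dose-limiting toxicity based on grade III or IV acute GvHD" and "Chronic extensive GvHD". The primary objective, in the synopsis and in section 2.1, covers both and names only the Glucksberg scale for grading and staging. Section 3.2, at the end of the follow-up list, is explicit: "Acute and chronic GvHD will be graded according to the Glucksberg scale (see Appendix 1".

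Appendix 1 is headed "Glucksberg acute GvHD scores". It gives organ stages, overall grades I to IV and the IBMTR index A to D. Appendix 3 gives a chronic GvHD classification, with five descriptions of limited disease and nine of extensive disease.

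In the synopsis visit schedule, the row "GvHD acc. to Glucksberg" is marked at screening and at weeks 2-4. Its cell for follow-up after the last infusion is blank, while physical examination and performance index are marked there. The follow-up list in section 3.2 (within one month, then three-monthly) agrees. It has history, examination, performance index, blood count, bilirubin and chimerism, but no GvHD item and no body weight. Eye and lung function tests are yearly, and other laboratory work follows institutional routine. Section 3.3 sets this observation at one year. Section 11 (Analysis) promises a cumulative incidence of extensive chronic GvHD.

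**The concern.** A primary endpoint needs an instrument that can produce it and visits at which that instrument is applied. On a literal reading, a site grading chronic GvHD by Appendix 1 records a grade from I to IV or an index from A to D. Neither can be turned into limited or extensive.

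A cumulative incidence also needs a dated onset and comparable ascertainment over the whole observation period. If extensive chronic GvHD is recorded only when someone notes it under history, examination or adverse events, the rate depends on site habit, and omissions lower it. In a study whose first objective is safety, that error makes the product look safer.

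**Working it through.** **Endpoint against instrument**

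| Place | What it fixes for chronic GvHD |
|---|---|
| Synopsis, section 2.3 | Extensive disease is a primary endpoint |
| Synopsis, section 2.1 | Glucksberg scale; no appendix cited |
| Section 3.2 | Glucksberg scale, Appendix 1 |
| Appendix 1 | Acute grades I-IV, IBMTR A-D; no limited/extensive category |
| Appendix 3 | Limited/extensive classification; not cited in sections 1-11 |

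Only Appendix 3 can yield the endpoint. The one cross-reference for chronic GvHD points to Appendix 1.

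**Endpoint against schedule**

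- The weeks 2-4 GvHD check also applies after the last infusion, because the schedule refers later infusions back to the first.
- On the schedule alone, the rest of the observation year has no GvHD grading: 52 - 4 = 48 weeks.
- If the first follow-up visit falls at month 1 and the others come three-monthly from there, they fall at months 1, 4, 7 and 10. These visits have an examination but no GvHD line.
- The two-weekly screening in section 3.1 has no stated end, but it uses the Glucksberg criteria of Appendix 1.
- Appendix 3 uses weight loss above 15% and, for liver involvement, "alkaline phosphatase >2 x upper limit of normal, AST or ALT >3 x upper limit of normal, or total bilirubin >1.6". Of these items only bilirubin is on the follow-up list.

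**Precision and the effect of a missed case**

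Section 11 (Confidence intervals for safety) tabulates interval widths for n = 20. With x = 20 × rate, the exact Clopper-Pearson interval runs from the α/2 quantile of Beta(x, 21 - x) to the 1 - α/2 quantile of Beta(x + 1, 20 - x). All 18 printed widths are reproduced, for example 0.379 at a rate of 0.20 and 0.305 at 0.10 (95%). The table was written for acute GvHD, but the formula holds for any proportion with n = 20.

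One missed case in an age group changes the rate by 1/20 = 5 points, or by 1/40 = 2.5 points in all 40 patients.

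| Cases recorded of 20 | Rate | 95% interval |
|---|---|---|
| 4 | 20% | 0.057 to 0.437 |
| 3 | 15% | 0.032 to 0.379 |
| 2 | 10% | 0.012 to 0.317 |

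The protocol gives neither an incidence of extensive chronic GvHD nor a detection probability, so the next figures rest on assumptions. With true incidence p and detection probability s, the chance of recording no case among 20 is (1 - ps)^20.

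| Assumed p | s = 1 | s = 0.75 | s = 0.5 |
|---|---|---|---|
| 10% | 12.2% | 21.0% | 35.8% |
| 20% | 1.2% | 3.9% | 12.2% |
| 30% | 0.1% | 0.6% | 3.9% |

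**Stool volume, as a limitation only**

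Appendix 1 stages gut involvement in fixed volumes ("Stage 1: Diarrhea 500-999 mL/day") for ages above 0 to below 80. At assumed weights, 500 mL/day is 500/70 = 7.1 mL/kg at 70 kg and 500/10 = 50 mL/kg at 10 kg.

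**The case against.** The strongest reply is that this is one wrong cross-reference. Appendix 3 is in the protocol, the word extensive is defined only there, and an experienced transplant physician would use it. That stands against any claim that the endpoint is undefined. It does not remove the contradiction, because section 3.2 directs chronic GvHD elsewhere in so many words.

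Second, follow-up is not empty. History, examination, performance index and bilirubin are obligatory, eye and lung tests are yearly, routine care may supply liver enzymes, and clinical adverse events go on the CRF. This stands too. A reader might infer that the follow-up year has no assessment at all, and the documents do not support that. What is missing is a scheduled GvHD grading and some of the data it needs.

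Third, a reader might infer that Appendix 3 sets two competing liver thresholds for the endpoint. It does not. The limited and extensive definitions agree with each other, and the higher values stand in a list of signs that could indicate chronic GvHD. The liver entry among the diagnostic indicators refers back to the limited and extensive definitions.

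Fourth, a reader might infer from the stool volumes that children are under-staged. The arithmetic shows unequal volumes per kilogram, but under-staging needs a paediatric norm that the protocol does not give. Skin, liver and performance status also enter the grade, and gut stage 4 needs no volume.

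**Conclusion.** The point holds as a contradiction between sections plus a gap in the schedule. The text names an acute instrument for a chronic endpoint, leaves the fitting classification uncited, and lists no GvHD grading at the quarterly visits after the last infusion. Extensive chronic GvHD would be captured unsystematically and probably under-counted.

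Each missed case costs 5 points per age group of 20. The number of missed cases cannot be derived from the protocol, and the detection scenarios above are illustrations. The direction, towards too low a rate, assumes that unscheduled recording loses more true cases than it adds false ones.

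The fixed stool volumes are a limitation to state when paediatric acute GvHD rates are reported or set beside those of adults. They do not show that children are graded wrongly.

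**What to change.** 1. Reconcile the primary objective (synopsis and section 2.1) and the grading sentence in section 3.2 with the appendices: acute GvHD graded by Appendix 1, chronic GvHD classified as limited or extensive by the definitions in Appendix 3.
2. Add acute and chronic GvHD status with date of onset, body weight and ALP/AST/ALT to the obligatory visits after the last infusion, both in the schedule table and in the section 3.2 list.
3. State as a limitation that the gut stages use volumes not scaled to body weight. No change to the stages is proposed, because aGvHD grades also decide whether infusions continue (sections 3 and 8.1).

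The cost is a protocol amendment, one CRF page and a few laboratory values from blood draws that already take place. The observed GvHD rate may come out higher, as a result of more complete ascertainment.

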### **3.3 Study Duration**

The estimated duration of the recruitment period will be 3 years and the total duration of the study is expected to be at least 5 years.

The study duration per patient will include study phase during CIK cell infusions and observational phase after the last CIK cell infusion.

Study phase will last until the patient reaches molecular remission (= end of CIK cell infusions), progresses or until the patient has received a maximum of 8 CIK cell infusions (maximum duration of study phase 1 year).

Observational phase will last 1 year after the last CIK cell infusion.

Additionally, CIK cell infusions will be terminated if the patient meets discontinuation criteria (see chapter 8.1). "Off-protocol" patients will be followed up for another 28 days. Patients where CIK cell infusions are discontinued, but who stay in the protocol will be followed up for 1 year (see chapter 8.1).

### **3.4 Number of Patients**

40 Patients will be included into the study. The aim is to include 20 patients in each group that is 20 children and 20 adults.

## **4 Study Population**

Acute leukemia and MDS patients aged >0 and <80 years of both gender experiencing molecular relapse after allogeneic stem cell transplantation.

It is known that the amount of leukemia cells is very critical for every type of immunotherapy. As a consequence, chemotherapy is needed to reduce the percentage of leukemia blast cells below 5%. And for this, patients need to be "eligible for chemotherapy" in terms of their general medical condition. Antineoplastic chemotherapy however, is necessary to bring patients, with frank hematological relapse after allogeneic stem cell transplantation, in complete hematological

remission (<5% of leukemia blasts in the bone marrow) before immunotherapy may be started.

All chemotherapy given for remission induction is not part of the study.

Chemotherapy has to be stopped 3 days before CIK cell infusions could be given.

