**Legend:**

( ), if applicable/optional

$x^1$ , monitoring for acute transfusion related toxicity while and up to 12 hours after CIK cell infusion, patients should be observed overnight within the context of an inpatient hospital stay. The study drug must be administered where emergency resuscitative equipment and personnel trained in the management of anaphylaxis are immediately available to treat systemic reactions under the direct supervision of a physician

$x^2$ , blood samples before, 1 hour, 1 and 2 weeks after CIK cell infusion for analyses of cytotoxic effects and tumor escape mechanisms

$x^3$ , monthly obligatory

$x^4$ , every 3 months

$x^5$ , optional

$x^6$ , once a year

$7$ , stop of CIK cell infusions: in case of molecular remission or if discontinuation criteria are reached,

If the patient does not reach molecular remission, administration of CIK cells will be stopped after the 8th CIK cell infusion.

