# 1 Introduction

## 1.1 Allogeneic Stem Cell Transplantation and Cellular Therapy

In acute lymphoblastic (ALL) and myeloid (AML) leukemia patients as well as in adult myelodysplastic syndrome (MDS) patients with chemotherapy resistant diseases allogeneic hematopoietic stem cell transplantation (SCT) will be performed according to the respective study protocols. Moreover, allogeneic SCT includes upfront therapy for pediatric patients with MDS, and will also be offered for therapy-related MDS and AML, which might occur as complications of chemotherapy. This complication often presents after a median latency period of approximately four to five years after chemotherapy treatment.

Standard therapy of BCR-ABL positive leukemias above all includes treatment with tyrosine-kinase inhibitors (TKI).

Hence, allogeneic SCT has become an established method in the treatment of above-mentioned high-risk leukemia and myelodysplastic syndromes (MDS). In both groups, the therapeutic success is limited by patients' relapse. Once a stem cell recipient relapses, further therapeutic options are limited. For instance, re-induction chemotherapy may cause remission with acceptable toxicity and a possible delay in time to relapse but therapeutic effects are transient. Relapsed patients with good performance status and without severe comorbidity might be considered for a second allogeneic SCT, if relapse occurs after day 300 in adult and after day 200 in pediatric patients. In these patients, second allogeneic SCT may provide a small curative chance of 20% but this approach entails a high rate of morbidity and mortality.

Another treatment option may include taper of immunosuppressive medications followed by donor lymphocyte infusion (DLI), which can generate a graft versus leukemia effect (GvL), but is associated with an increased risk of graft versus host disease (GvHD). Moreover, the success rate of this approach is less than 15%.

To improve outcome of leukemia and MDS patients after allogeneic SCT, the detection of impending relapse or early stages of relapse is necessary, as this status is a precondition for further therapeutic options. Predictors of relapse after allogeneic SCT have been monitoring for minimal residual disease (MRD), and BCR-ABL as well as loss of donor cell chimerism.

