#### 4.1 Inclusion Criteria

- Acute leukemia and MDS patients with detectable MRD,  $\geq 10^{-4}$  of BCR-ABL/ABL ratio, or MC in PB or BM samples obtained during monitoring for relapse after allogeneic stem cell transplantation.
- Detectable MRD, or  $\geq 10^{-4}$  of BCR-ABL/ABL ratio .
- Acute leukemia and MDS patients with MC  $\geq 1\%$  of autologous signals in PB samples confirmed by another PB or BM sample within one week. Patients with MC  $\geq 1\%$  of autologous signals in CD33+ and/or CD34+ subpopulations in PB samples confirmed by BM analyses within one week. Acute leukemia and MDS patients with MC  $\geq 1\%$  of autologous signals including signals in CD33+ and/or CD34+ subpopulations in BM samples.
- Patients without immunosuppressive agents and steroids.
- Patients without chemo- or immune therapy, except patients with tyrosine-kinase inhibitors (TKI) for treatment of BCR-ABL positive leukemias.
- Patients with < grade II GvHD.
- Patients with Karnowsky or Lansky performance status  $\geq 50\%$ .
- Patients and/or his/her legal representative having reviewed the patient information/informed consent form and have had their questions answered and have given written informed consent.

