### **4.3 Allowed/prohibited concomitant therapies**

Except for patients with BCR-ABL positive leukemia, no concomitant anti-neoplastic treatment is allowed. In the BCR-ABL positive leukemia patients tyrosine kinase inhibitors (TKI) are the standard treatment to control the disease. However, there is no cure possible with TKI as single treatment. As a consequence, these patients may be included into the study while receiving TKI during the CIK cell treatment.

In all other patients' concomitant antineoplastic therapy is not allowed. Antineoplastic chemotherapy however, is necessary to bring patients, with frank hematological relapse after allogeneic stem cell transplantation, in complete hematological remission (<5% of leukemia blasts in the bone marrow). Patients with molecular relapse who are still in hematological remission are eligible for this study.

All chemotherapy given for remission induction is not part of the study. Chemotherapy has to be stopped 3 days before CIK cell infusions could be given.

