**The following criteria lead to stop of additional CIK cell infusions; patients are remaining in the study:**

- Development of GVHD > Grade II
- Response to CIK cell therapy: If mixed chimerism was the reason for study eligibility, than the achievement of complete donor chimerism leads to the stop of further CIK cell infusions. If the inclusion into the study was favored by minimal residual disease detection, the achievement of MRD negativity leads to a stop of additional CIK cell infusions.

- Severe infections

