## Analysis

A descriptive statistics will be performed at the end of the study. An intent-to-treat principle (ITT) or per-protocol analysis will be done.

To analyze the efficacy of CIK cell treatment following factors will be considered:

- Complete and partial molecular response
- rate and duration of complete/partial molecular response following CIK cell administration at the end of CIK cell infusions and after 1 year of first CIK cell infusion
- rate of and time to non response
- rate of and time to relapse with previous partial/complete response
- Progression-Free survival (PFS) and overall survival (OS)
- Cumulative incidences of: haematological relapse/progression, deaths without relapse/progression
- Cumulative incidence of aGVHD > grade II and extensive chronic GvHD
- Median and range for the number of CIK cell dose and for cumulative dose CIK cells/kg for all patients, children and adults

- Median and range for cumulative T cells/kg according donor type (MSD, MUD,MMFD) that patient requires in the study

Complete molecular response is defined as the molecular remission: the Minimal Residual Disease not detectable (MRD < 10^-6) and Mixed Chimerism MC < 1%.

Partial response is defined as no molecular remission but not haematological relapse. Non response is defined as haematological relapse without previous or complete response.

The median of PFS and OS time will be estimated. Kaplan-Meier estimates will be used to estimate PFS probability and OS probability. Log-rank test will be used as appropriate. For PFS will be considered as events: disease progression or relapse, death without relapse/progression and secondary neoplasm. For OS death from any cause will be considered an event.

Gray-Model will be used for cumulative incidences. Patients lost to follow-up without event will be censored at the date of their last follow up evaluation.

PFS, OS and cumulative incidences will be estimated after 1 year initiation of CIK cell therapy and after 1 year until the last CIK cell infusion.

If the data meet the necessary requirements, longitudinal analysis will be conducted to explore the improvement of hematologic and immune reconstitution of leucocyte, CD3-, CD4-, CD8-, CD56-, and CD14-positive cells until the first year after begin of the CIK cells therapy.

The dynamic of cytokine profile during cell infusion and tumor escape mechanisms following CIK cell infusion will exhibit in curves over the time.

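### Chemotherapy may end 3 days before the first CIK infusion, but no post-chemotherapy positive marker is explicitly required and complete response has no baseline, so in re-induced patients chemotherapy effect can be credited to CIK cells

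*Protocol*

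**What the plan says.** Sections 4 and 4.3 state that patients in frank haematological relapse need chemotherapy to bring marrow blasts below 5% before immunotherapy, that this chemotherapy lies outside the study, and that "Chemotherapy has to be stopped 3 days before CIK cell infusions could be given". Section 4.3 adds: "Patients with molecular relapse who are still in hematological remission are eligible for this study".

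Section 4.1 asks for detectable MRD, a BCR-ABL/ABL ratio of at least 10^-4, or "MC in PB or BM samples obtained during monitoring for relapse after allogeneic stem cell transplantation". Its only time rule is that mixed chimerism in peripheral blood be confirmed within one week. Sections 4.1 and 4.2 also require patients to be without chemotherapy, but give no interval.

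Section 11 (Analysis) says: "Complete molecular response is defined as the molecular remission: the Minimal Residual Disease not detectable", with MC below 1% as a second condition. Partial response is any state short of molecular remission without haematological relapse. Response is rated "following CIK cell administration at the end of CIK cell infusions and after 1 year of first CIK cell infusion". Under Section 8.1, for a patient enrolled on mixed chimerism, "the achievement of complete donor chimerism leads to the stop of further CIK cell infusions"; MRD negativity does the same for a patient enrolled on MRD.

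**The concern.** The trial has one arm, and molecular response is its efficacy endpoint (Section 2.4). Without a control group, a response can be attributed to CIK cells only if the pre-infusion state is known and no other recent treatment explains the change. Section 1.1 says of re-induction that "re-induction chemotherapy may cause remission with acceptable toxicity and a possible delay in time to relapse but therapeutic effects are transient". A patient whose chemotherapy ended days before the first infusion may therefore reach molecular remission, or relapse later, partly because of that chemotherapy.

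At stake are the complete-response rate at end of infusions, response duration and PFS in re-induced patients. Section 11 intends the results to inform a larger study, and the bias acts in one direction only.

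**Working it through.** **1. Can re-induced patients enter?** Yes. Sections 4 and 4.3 describe the route, and Section 4.2 excludes haematological relapse only when it occurs before day 120 after transplantation. In the earlier series in Section 1.5, 3 of 14 patients were relapsed and treated with or without chemotherapy. Entry rules differed there, so this shows that the route exists and does not estimate its share here.

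**2. Is a positive post-chemotherapy marker required?** Not in so many words. Sections 3.2, 4 and 4.3 describe current molecular relapse, and Section 3.1 gives the first dose once all criteria are met. No sentence ties the positive result to a sample after the last chemotherapy dose. In the Synopsis schedule, chimerism is marked at screening, MRD and BCR-ABL are marked there as if applicable/optional, and none of the three is marked at week 0.

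**3. Does the response definition use a baseline?** No. MRD not detectable and MC below 1% is a state at the time of reading.

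**4. Earliest gap from last chemotherapy dose to a response reading.** These are lower bounds, because 3 days is a minimum.
- Peripheral-blood chimerism at the 2-4 week visit (schedule footnote: "monthly obligatory"): 3 + 14 = 17 days to 3 + 28 = 31 days, after one infusion at the starting dose.
- Marrow MRD every 3 months, taken as 13 weeks: 3 + 91 = 94 days, after 3 infusions (weeks 0, 6, 12) or 4 (weeks 0, 4, 8, 12).

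Complete response needs both conditions. The 17-31 day reading can therefore satisfy the definition only in a patient enrolled on mixed chimerism with no MRD marker assessed. In that patient it also stops infusions, so it becomes the end-of-infusions rating. Otherwise the first scheduled marrow MRD, at about 3 months, is needed.

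**5. Weight of one patient.** The protocol's intervals reproduce as exact (Clopper-Pearson) 95% limits. At rate 0.2, 8/40 has width 0.266 and 4/20 has width 0.379, as printed. One misattributed complete response adds 1/40 = 2.5 points or 1/20 = 5 points:

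| Responders | Exact 95% CI |
|---|---|
| 8/40 | 0.0905-0.3565 |
| 9/40 | 0.1084-0.3845 |
| 4/20 | 0.0573-0.4366 |
| 5/20 | 0.0866-0.4910 |

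**6. Range under assumptions.** Let r be the true CIK complete-response rate, f the share re-induced, and q the share of those in molecular remission from chemotherapy. The expected number of extra responders is 40 × f × q × (1 − r). None of the three is in the protocol. With r = 0.2:
- f = 0.10, q = 0.20: 40 × 0.10 × 0.20 × 0.8 = 0.64 patients.
- f = 0.25, q = 0.50: 40 × 0.25 × 0.50 × 0.8 = 4 patients, so 8/40 becomes 12/40 (30%; CI 0.166-0.465).
- f = 0.50, q = 0.50: 40 × 0.50 × 0.50 × 0.8 = 8 patients.

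**7. What is not touched.** A re-induced patient with a persisting marker and no haematological relapse already counts as a partial responder, so the combined complete/partial rate used for the sample size hardly changes. It is not wholly immune, because chemotherapy may also delay haematological relapse. The primary GvHD endpoints do not use the marker.

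**The case against.** The best counter-argument is that the protocol treats eligibility as one current state. Section 3.2 puts molecular relapse and fewer than 5% malignant cells in the same criterion. A frankly relapsed patient can show the low blast count only after chemotherapy. Infusions stop at molecular remission, so starting them in a marker-negative patient would contradict the design. If every patient enters marker-positive, reaching the defined state is already conversion. Section 2.2 (reduction or disappearance of MRD) and Section 8.1 (response judged on the qualifying marker) point the same way.

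Most of this stands. A reader might infer that the protocol admits patients already cleared by chemotherapy. No text permits that; the gap is a missing explicit requirement. A reader might also infer that any re-induced patient can be declared a complete responder within 17-31 days. The joint MRD and chimerism condition rules that out, except where no MRD marker is assessed.

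The objection does not reach a marker that is positive at entry but still falling after chemotherapy that ended as little as 3 days earlier. It also leaves PFS and time to relapse open to the delay that Section 1.1 describes. Nor can the sample timing be left to a later analysis plan, because a sample that was never required cannot be recovered.

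**Conclusion.** The point holds and is minor. The stated rules let chemotherapy effect be credited to CIK cells in re-induced patients, chiefly in the complete-response rate at end of infusions, response duration and PFS. Less carry-over is expected at 1 year, since Section 1.1 calls re-induction effects transient.

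The total bias cannot be derived, because the number of re-induced patients is not stated. Only the weight per patient is fixed: 2.5 points at n=40, 5 points at n=20. Four such patients (assumed) would add 10 points overall, or 20 if all were in one age group. Both are below the planned interval widths at rate 0.2 (26.6 and 37.9 points), but always upward.

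A reader might conclude that the efficacy analysis as a whole, or its planned precision, is invalid. The documents do not support that: the study is declared explorative, the complete/partial rate behind the precision tables is largely unaffected, and so are the primary endpoints.

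**What to change.** 1. In Section 4.1, require the qualifying MRD, BCR-ABL or mixed-chimerism result to be positive in a sample taken after the last chemotherapy dose and before the first CIK infusion. The marrow already needed to show fewer than 5% blasts can serve.
2. In Section 11 (Analysis), define complete molecular response as conversion from that sample to MRD not detectable and MC below 1%.
3. Show complete response, PFS and relapse by re-induced yes/no as a supportive display, because item 1 cannot exclude a marker that is still falling. Keep all patients, and children and adults separately, as the main analysis.

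The cost is one eligibility sentence, one clause in the response definition, and a descriptive table with the chemotherapy date and prior relapse recorded to support it. A few re-induced, marker-negative patients would not qualify. The subgroups will be small: if 4 or 12 of 40 were re-induced (assumed), the exact 95% interval would be 0.068-0.932 at 2/4 and 0.211-0.789 at 6/12, so the display can only be descriptive.
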